#### Statistical analysis

The data is first evaluated visually based on standard techniques including quantile-quantile plots and histograms to detect possible outliers and to assess the normality. Normality is also evaluated using Shapiro-Wilk test and logarithm or other statistical transformations are performed when appropriate. The data is also analyzed for possible dimensionality reduction using standard methods such as principal component analysis.

Statistical analyses are performed using hierarchical mixed linear models. The models include two within-factors: time (before and after intervention) and twin (heavier and leaner co-twin), and their interaction term (time x twin). Medications, adherence to the exercise intervention, sex, age, BMI and other factors are included in the models when appropriate. The potential covariates will be screened for association, and covariates that do not show significant association with the response variable will be excluded from the analysis. When the number of participants allows it, we will carry out separate subgroup analyses by sex, age (two younger cohorts vs. older cohort), and/or mass (obese vs. non-obese participants). Subjects with missing data points are included in the statistical analysis by using the restricted maximum likelihood estimation within the linear mixed models. Hence, model-based means and 95% confidence intervals are reported.

Correlation analysis are performed using Pearson’s product-moment correlation coefficient for normally distributed data and Spearman’s rank correlation coefficient for non-normally distributed data. All statistical tests are performed as two-sided and *p*-values less than 0.05 will be considered as statistically significant.

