**Methods:**

CROSSYS is an exercise training intervention, in which participants are monozygotic twins from pairs discordant for body mass index (BMI) and within a pair at least the other is overweight. Twins are recruited from three population-based longitudinal Finnish twin studies, including twins born in 1983–1987, 1975–1979, and 1945–1958. The participants undergo 6-month-long exercise intervention period, exercising four times a week (including endurance, strength, and high-intensity training). Before and after the exercise intervention, comprehensive measurements are performed in Turku PET Centre, Turku, Finland. The measurements include: two positron emission tomography studies (insulin-stimulated whole-body and tissue-specific glucose uptake and neuroinflammation), magnetic resonance imaging (brain morphology and function, quantification of body fat masses and organ volumes), magnetic resonance spectroscopy (quantification of fat within heart, pancreas, liver and tibialis anterior muscle), echocardiography, skeletal muscle and adipose tissue biopsies, a neuropsychological test battery as well as biosamples from blood, urine and stool. The participants also perform a maximal exercise capacity test and tests of muscular strength.

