**Discussion:**

This study addresses the major public health problems related to modern lifestyle, obesity, and physical inactivity. An eminent strength of this project is the possibility to study monozygotic twin pairs that share the genome at the sequence level but are discordant for BMI that is a risk factor for metabolic impairments such as insulin resistance. Thus, this exercise training intervention elucidates the effects of obesity on metabolism and whether regular exercise training is able to reverse obesity-related impairments in metabolism in the absence of the confounding effects of genetic factors.

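### BMI is a permitted, significance-screened covariate in models whose heavier/leaner factor is itself the within-pair BMI ranking, so the twin main effect can stop estimating the effect of obesity

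*Protocol article*

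**What the plan says.** Three statements in the protocol article's Statistical analysis section have to be read together.

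- The core model: "The models include two within-factors: time (before and after intervention) and twin (heavier and leaner co-twin), and their interaction term (time x twin").
- The covariates: "Medications, adherence to the exercise intervention, sex, age, BMI and other factors are included in the models when appropriate".
- The selection rule: "covariates that do not show significant association with the response variable will be excluded from the analysis". No separate level is given for this screen. The section's general threshold is p-values "less than 0.05 will be considered as statistically significant".

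The meaning of the twin factor follows from recruitment. In the Abstract, "participants are monozygotic twins from pairs discordant for body mass index (BMI"). The Background asks for a within-pair difference of at least 2 kg/m2. The Participants section words this as a BMI difference and/or insulin resistance.

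The Abstract's Discussion says the study "elucidates the effects of obesity on metabolism and whether regular exercise training is able to reverse obesity-related impairments in metabolism". The Power calculation section names two tests: the change over time, and whether that change differs between heavier and leaner twins. BMI is among the body composition measures taken before and after training. The article does not say which of the two values would enter a model.

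**The concern.** The twin factor orders each pair by BMI. Entering BMI beside it asks how heavier and leaner co-twins would differ at equal BMI. That is not the effect of obesity, and it is a comparison that BMI-discordant pairs do not supply within the pair.

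The screening rule works in the wrong direction. BMI fails the screen when it is unrelated to the outcome, where including it would do little harm. It passes when outcome and BMI are related, which is where there is a heavier-leaner difference to lose. The Background itself links obesity to insulin resistance, and insulin-stimulated glucose uptake (whole-body and tissue-specific) is the named primary outcome measure.

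At stake is the reading of the twin main effect. A real obesity-related difference could be reported as absent, for some outcomes and not others, depending on which models happened to keep BMI.

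**Working it through.** The plan states no figure for this point, so there is none to reproduce. The check is algebra, followed by an illustration with assumed inputs.

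**Algebra.** Code twin as 0 (leaner) or 1 (heavier) and time as 0 or 1. The twin coefficient is then the heavier-leaner difference before training, and the time coefficient is the leaner twin's change. With complete data and the time x twin interaction in the model, the four fitted cell means equal the observed ones. If b is the estimated BMI slope:

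- adjusted twin = total twin difference - b x (mean BMI gap);
- adjusted time = total change - b x (mean BMI change in the leaner twin);
- adjusted time x twin = total interaction - b x (heavier minus leaner mean BMI change).

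Baseline BMI does not change over time, so both change terms are zero and only the twin coefficient moves. With time-varying BMI all three can move.

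**Inputs.** From the article: 30 completing pairs (Participants), two co-twins, two time points, two-sided 0.05. Assumed, since the documents do not give them:

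- within-pair BMI gap at least 2, mean 6 kg/m2;
- outcome slope -0.25 per BMI unit, the same within and between pairs;
- BMI change -0.5 in leaner and -1.5 in heavier twins;
- adherence 5 points lower in the heavier twin, with 0.02 outcome units of change per point;
- SDs: pair 1.0, person 0.7, residual 0.7.

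**Results**, 2000 simulated trials, generalised least squares with the pair and person covariance:

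| Covariate added | Twin (SE) | Twin rejected | Time | Time x twin |
|---|---|---|---|---|
| None | -1.50 (0.26) | 100% | 0.63 | 0.155 |
| Baseline BMI | 0.00 (0.37) | 5% | 0.63 | 0.155 |
| Time-varying BMI | 0.00 (0.36) | 5% | 0.50 | -0.096 |
| Adherence, main effect | -1.45 (0.27) | 99.9% | 0.63 | 0.155 |
| Adherence and adherence x time | -1.50 (0.27) | 99.9% | 0.58 | 0.25 |

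The formulas reproduce the BMI rows:

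- twin: -1.50 - (-0.25 x 6) = 0.00;
- time with time-varying BMI: 0.63 - (-0.25 x -0.5) = 0.63 - 0.125 = 0.505, against 0.50 simulated;
- time x twin with time-varying BMI: 0.155 - (-0.25 x -1.0) = -0.095, against -0.096 simulated.

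Within pairs, BMI and the twin indicator correlate at about 0.91 (variance inflation about 6).

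**Range.** At slope -0.25, adjustment removes 0.25 x 2 = 0.5 outcome units for a mean gap of 2, and 0.25 x 10 = 2.5 for a mean gap of 10. A second set of assumptions (30 pairs, mean gap 4 to 5, slope -0.2, 600 runs) gives -0.83 to -1.04 without BMI, and -0.02 to 0.01 with it.

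**The case against.** The strongest reply is that the Power calculation section names time and time x twin as the tests, and baseline BMI as a main effect leaves both alone. This stands, and it limits the point. A reader might infer that the training tests themselves are adjusted away. The documents do not support that: it would need time-varying BMI or a covariate-by-time term, and the article states neither. It does not rule them out either. The twin main effect still matters, because the Abstract's Discussion names the effect of obesity as an aim.

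A reader might also infer that adherence erases the heavier-leaner contrast. It does not: as a main effect it moves twin only from -1.50 to -1.45. It is measured after baseline, and the article's Discussion says it will be taken into account, but it shifts the training contrasts only if interacted with time.

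The inclusion qualifier and an unseen analysis plan might keep BMI out, and the exclusion rule does not literally promise to keep every associated covariate. Both are true. But BMI is named, no sentence bars it from models with the twin factor, and no unadjusted model is named as the main one.

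The zero after adjustment is built into the simulation, which generates the outcome from BMI with no separate twin effect. That is fair, so the zero illustrates and does not predict. If slopes differ within and between pairs, the adjusted coefficient is a mixture that need not be zero but is still not the obesity effect.

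Pairs may also qualify on insulin resistance, so some BMI gaps may be small. That reduces the amount removed and the collinearity, but not the direction. Sex and age are shared within a pair and cannot distort the within-pair contrast.

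A claim that screening makes the confidence intervals too narrow is a general worry about selecting covariates on the same data. It was not quantified here and is not relied on.

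**Conclusion.** The point holds for BMI and the screening rule. As written, the plan permits a model in which the twin main effect no longer estimates the obesity effect, and its selection rule favours that model where obesity matters. The loss equals the BMI slope times the mean BMI gap. It is complete if the outcome depends on BMI with a common slope (-1.50 to 0.00 in the illustration) and partial or distorted otherwise. The sizes rest on assumed slopes, gaps and SDs. The existence of the shift needs only a non-zero estimated BMI slope.

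For time and time x twin the point is conditional. They are essentially unaffected by baseline BMI as a main effect, exactly so in complete data. They are affected by time-varying BMI, which takes out the part of the training effect that runs through weight change. Adherence is secondary.

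**What to change.** Amend the Statistical analysis section as follows.

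1. Name the main model: time, twin and time x twin, without individual BMI (baseline or time-varying) and without adherence.
2. If differences in BMI between pairs are to be accounted for, use the pair's mean baseline BMI. It is the same for both co-twins and leaves the within-pair contrast intact.
3. Replace the significance screen with one prespecified covariate set for all outcomes, for example sex, age and baseline medication.
4. Report BMI-adjusted models as labelled secondary mediation analyses, stating which BMI value is used. Report adherence as a labelled secondary dose-response analysis (adherence x time). Whether training acts independently of weight change is a legitimate question, but a different one.

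The cost is a few sentences, with no new data and no burden on participants. The downside is a few degrees of freedom spent on covariates that may prove weak.

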### Participants

The participants of the CROSSYS study are monozygotic (MZ) twin pairs that are recruited from three unique population-based longitudinal twin studies [35–37]. Of these three cohorts, the two younger cohorts consist of twins from the FinnTwin12 (FT12, twins born 1983–1987) and FinnTwin16 (FT16, twins born 1975–1979) studies, and twins born in 1945–1957, who form part of the older cohort from the Finnish Twin Cohort Study, twins born in 1945–1957 (Fig. 2). The three cohorts consist altogether of more than 9200 twin pairs, of which 1/3 are MZ. All twins have been identified through Finland’s central population registry, permitting exhaustive and unbiased ascertainment of all twins living and resident in Finland. A total of 54 MZ pairs discordant for BMI and/or insulin resistance have participated previously to the TwinFat study in the University of Helsinki, and their monozygocity has been confirmed by the genotyping of 10 informative genetic markers [38]. All these 54 pairs are invited to participate in the present study. Inclusion criteria are: MZ twins, BMI within-pair difference ≥ 2 kg•m^− 2^ and/or insulin resistance, and at least one of the co-twins is overweight (BMI > 25 kg•m^− 2^). Exclusion criteria are: BMI > 60 kg•m^− 2^, body mass > 170 kg, waist circumference > 150 cm (due to the gantry limitations of PET and MRI machines), mental disorder or poor compliance, eating disorder or excess use of alcohol, active ulcus disease, diabetes requiring insulin treatment or fasting glucose > 10 mmol•l^-1^, pregnancy, past dose of radiation, claustrophobia, presence of ferromagnetic objects that would make MRI contraindicated, physical disability that would prevent exercising, or any other ﻿condition which could potentially endanger participant’s health during the study or interfere with the interpretation of the results. It is estimated that 25% of twins do not want to participate or are not eligible to the study and another 25% will drop out during the intervention. Hence, 30 twin pairs are expected to successfully complete the study.

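### Separate sex and age-cohort analyses, with no subgroup-by-time interaction named, cannot show whether the training response differs between subgroups

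*Protocol article*

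**What the plan says.** All of this is in the protocol article. In the Statistical analysis section:

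- The subgroup method, for use only if enough participants are available, is "we will carry out separate subgroup analyses by sex, age (two younger cohorts vs. older cohort), and/or mass". So the analyses are conditional on numbers, and not all need be done.
- The mixed model has time and twin (heavier or leaner) as within-factors "and their interaction term (time x twin"). This is the only interaction named.
- Sex and age otherwise enter as covariates: "sex, age, BMI and other factors are included in the models when appropriate". Candidates without a significant association with the response are dropped.
- The decision rule is general: "All statistical tests are performed as two-sided and *p*-values less than 0.05 will be considered as statistically significant".
- Model-based means with 95% confidence intervals are to be reported.

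The Participants section gives the expected size: "Hence, 30 twin pairs are expected to successfully complete the study". The Power calculation section sets out two questions: whether means change over time, and whether that change differs between heavier and leaner co-twins.

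**The concern.** Two separate analyses each ask whether training had an effect in that subgroup. Neither asks whether the effects differ. Results such as a p-value below 0.05 in women and above it in men can arise from subgroup size and chance alone, and the within-subgroup means and intervals still give no interval for the difference.

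The plan treats a parallel question differently. For heavier versus leaner co-twins it fits an interaction. For sex and age it splits the sample, although monozygotic co-twins share sex and age, so pairs stay intact and the interaction fits directly into the same mixed model. (The mass split is left aside here because co-twins can fall into different mass groups.)

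At stake is the reading of subgroup results from a sample of about 30 pairs. A sex- or age-specific training response could be inferred where none exists, and a real difference would be left without an estimate.

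**Working it through.** **The plan's own figure.** There is none on this point. The article states no power, no subgroup sizes and no error rate for subgroup comparisons.

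**Inputs.** From the article: 30 expected completing pairs (54 × 0.75 × 0.75 = 30.4) and two-sided alpha 0.05. Assumed: whole-sample power of 80%, 90% or 95%; splits of 15/15, 20/10 and 22/8 pairs; the same true effect in both subgroups; and a one-sample t-test on a pair-level contrast (mean change, or co-twin difference in change) as a proxy for the mixed model.

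**Step 1, effect size.** Power comes from the noncentral t distribution with n − 1 degrees of freedom and noncentrality d√n. Solving at n = 30 gives d = 0.53, 0.61 and 0.68 for 80%, 90% and 95% power.

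**Step 2, discordance.** With subgroup powers p1 and p2, the chance that exactly one subgroup is significant is p1(1 − p2) + p2(1 − p1).

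| Whole-sample power | 15/15 | 20/10 | 22/8 |
|---|---|---|---|
| 80%: p1, p2 | 0.48, 0.48 | 0.61, 0.32 | 0.66, 0.25 |
| discordant | 50% | 54% | 58% |
| 90%: p1, p2 | 0.60, 0.60 | 0.74, 0.41 | 0.78, 0.32 |
| discordant | 48% | 54% | 60% |
| 95%: p1, p2 | 0.69, 0.69 | 0.82, 0.49 | 0.86, 0.38 |
| discordant | 43% | 51% | 58% |

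For equal halves the expression is 2p(1 − p), which cannot exceed 50%. Unequal splits can exceed it.

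**Step 3, the alternative.** In simulated data with identical effects (100,000 runs per setting), the two-sample comparison of change, which is the subgroup-by-time interaction, was significant in about 5% of runs. Separate tests on the same data were discordant at the rates in the table.

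**Step 4, the article's planning inputs.** The rate depends heavily on effect size, so each planned outcome was checked at 30 pairs. Where SD and correlation are used, the SD of the difference is SD × √(2(1 − r)).

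- *M-value* (30% of 6.2 = 1.86, SD 0.3, r 0.7): 0.3 × √0.6 = 0.232, so d = 1.86/0.232 = 8.0. Both subgroups are always significant; discordance is about 0%.
- *VO2max* (taking the stated 6 pairs as 80% power): d = 1.43; discordance is 0.1% at 15/15 and 6.7% at 22/8.
- *Liver fat, inputs as printed* (20% of 2.1 = 0.42, SD 1.39, r 0.98): 1.39 × √0.04 = 0.278, so d = 1.51; discordance is 0.05% at 15/15 and 4.7% at 22/8.
- *Liver fat, taking the stated 22 pairs as the 80% power size*: d = 0.63; discordance is 47% at 15/15 and 54% at 20/10. Taken as 90% power: 38% and 48%.

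The two liver-fat readings conflict because the printed inputs give 6 pairs at 80% power, not 22. That is a separate matter, but it means neither reading can be relied on alone.

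**The case against.** The strongest reply is that the article never says subgroup p-values will be set against each other, and its stated inferential questions do not include whether sex or age changes the response. The analyses apply only when numbers allow, which may rule out subgroups as small as 8 or 10 pairs. The Power calculation section gives its model terms as a minimum, so further terms are not excluded, and a full analysis plan may add an interaction. Confidence intervals are promised as well as p-values. And at the planning effects for M-value and VO2max, discordance would be rare.

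Most of this stands, and it limits the claim. A reader might infer that the plan will produce false sex- or age-specific responses about half the time. The documents do not support that: they state no power, they do not describe comparing significance, and their own inputs put the rate near zero for M-value. A reader might also infer that interaction testing was considered and rejected. The article is silent on that.

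The reply does not remove the core point. Separate analysis is a stated method, not an omitted detail, and it does not estimate a difference at any power; within-subgroup intervals do not fill that gap. The low rates also cover only a few outcomes at favourable effects. The article says sample sizes could not be calculated for all main parameters, and it shows none for tissue-specific glucose uptake, a primary outcome, or for the time by twin contrast. Moderate power is plausible there.

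**Conclusion.** The point holds as a defect of method. Where the sex and age-cohort analyses are done as described, they cannot show that the training response differs between subgroups, and they yield no estimate or interval for that difference. This depends on no numerical assumption.

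The size of the risk is conditional. If the separate results were read by comparing significance, an identical response would look discordant in about 43-60% of cases. That range assumes 80-95% whole-sample power, 30 complete pairs, splits from 15/15 to 22/8 and a t-test proxy. It falls to about 0% for M-value at its planning effect, and to at most about 7% for VO2max (taking 6 pairs as 80% power) and for liver fat on its printed inputs. The change should be made, but it concerns conditional subgroup analyses and not the main test of training.

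**What to change.** Where subgroup analyses by sex or age cohort are done, fit them in the full-sample mixed model:

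- Add time by sex and time by cohort. For the heavier/leaner question, also add time by twin by sex and time by twin by cohort.
- Base any statement that the response differs by sex or age on the interaction estimate with its 95% confidence interval.
- Report within-subgroup means and intervals from that same model, label them exploratory, and draw no conclusion from significance in one subgroup alone.

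The cost is wording and a few model terms, with no new data or participants. There are two downsides. First, the pooled model assumes a common residual variance unless it is allowed to differ by subgroup. Second, interaction tests have low power at this size. With noncentrality d/√(1/n1 + 1/n2) and 28 degrees of freedom, a subgroup difference as large as the assumed overall effect (d = 0.53 to 0.68) would be detected with about 24% power (22/8, d = 0.53) to 44% power (15/15, d = 0.68). Fewer subgroup statements will be possible, and a non-significant interaction should not be read as evidence of equal response.

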Given that the response to exercise training is heterogeneous and affected by genetic factors, this study utilizes a co-twin control method in order to exclude the confounding effects of genetic factors. To pursue this objective, we recruit monozygotic (MZ) twin pairs that are discordant for body mass index (BMI) (difference ≥ 2 kg•m^− 2^) and at least the other twin is overweight (BMI ≥ 25 kg•m^− 2^). MZ twins share same genes at sequence level, are of the same sex, age and share most of their childhood environment. Thus, they provide an ideal research design to study the effects of regular exercise training on physical performance and metabolic health outcomes, in which the confounding effects of genetic factors can be controlled [22]. Additionally, because twin pairs included into this study are discordant for BMI, it is possible to examine the interaction-effect of different baseline weight and long-term exercise while genetic factors are controlled.

Exercise training provides an effective protection against chronic diseases that are triggered by low-grade systemic inflammation, such as insulin resistance [23]. As a drug-free treatment option, exercise training could lead to significant reduction in treatment cost due to reduced need for medication and fewer complications due to the improved physical fitness. We have previously shown in the Turku PET Centre that only 2 weeks of exercise training has a positive effect not only on the metabolism of the skeletal muscle [24] but also that of the heart [25, 26], the brain [27], and the intestine [28] in healthy, insulin resistant or type 2 diabetic participants. We have also shown that short-time exercise training decreases ectopic fat in the pancreas [29], liver [30], in and around the heart [31] and increases microbial diversity and decreases microbiota content related to obesity and intestinal inflammation [32]. These short-term intervention studies suggest that already a short exercise training period exerts positive systems-level effects on the metabolism of various tissues. Thus, current evidence provided by our research group and others’ [33, 34] suggest that exercise is able to counteract the undesired disturbances in metabolism related to obesity and T2D. However, more specified evidence of the effects of exercise training on different tissues is still needed in overweight/obese people prone to develop metabolic diseases such as T2D.

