The eminent strength of the study is the possibility to study MZ twin pairs discordant for BMI. The co-twin-pairs share a similar genome at sequence level that enables us to study the effects of obesity and insulin resistance in conjunction with long-term exercise training without the confounding effects of genetic variation. All of the twins to be recruited in CROSSYS have participated in previous twin studies in the University of Helsinki. This enables us to use longitudinal data on the development of the obesity and the changes in habitual physical activity of the twins [38, 68]. Another great strength of the present study is the use of state-of-the-art medical imaging technologies, which makes it possible to study tissue-specific metabolism (brain, heart, liver, pancreas, intestine, bone, adipose and muscle tissues) and brain function in detail.

The potential limitation of the study is that the observed changes may reflect changes in the diet. In the present study, we aim to investigate the effects of exercise, and we ask the participants not to change their diet during the 6-month-long exercise intervention. We also advice the personal trainers to help the participants to maintain their diet and to avoid the increase of energy intake that often occurs when an untrained person starts to exercise [69]. On the other hand, we do not wish the participants to lose excessively mass due to reduced energy intake. To assess dietary habits during the course of the intervention, the participants fill out a food diary in the beginning, middle, and end of the intervention. Another possible limitation of the study may be a variation in the exercise training adherence. The major role of the personal trainers is to provide encouragement and support to the study participants. In addition, the researchers monitor the training adherence via PolarFlow service. However, it is expected that there are differences in the training adherence, and this will be taken into account when analyzing the results. The third limitation are the missing data points that are expected to occur due to problems in PET tracer production, malfunction of the imaging equipment, and other unforeseen events. To alleviate this major problem, missing data points are taken into account by restricted maximum likelihood estimation within the linear mixed models.

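### The obese/non-obese subgroup classifies individuals and is analysed separately, so pairs that straddle the cut-off are separated and the subgroup contrast is neither fully within-pair nor tested

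*Protocol article*

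**What the plan says.** The Statistical analysis section describes one main model for all pairs: "The models include two within-factors: time (before and after intervention) and twin (heavier and leaner co-twin), and their interaction term (time x twin"). It then adds subgroup work: "we will carry out separate subgroup analyses by sex, age (two younger cohorts vs. older cohort), and/or mass (obese vs. non-obese participants"). This part of the plan is conditional on size ("When the number of participants allows it"). The third split is worded by participant, the method is separate analyses, and no BMI cut-off for obesity is given. On incomplete data the section states: "Subjects with missing data points are included in the statistical analysis by using the restricted maximum likelihood estimation within the linear mixed models".

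The Background gives the purpose of the design: "this study utilizes a co-twin control method in order to exclude the confounding effects of genetic factors". The Discussion repeats it: "The eminent strength of the study is the possibility to study MZ twin pairs discordant for BMI". Under Participants, pairs qualify on a "BMI within-pair difference" of at least 2 kg/m² and/or insulin resistance, provided that "at least one of the co-twins is overweight".

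**The concern.** Two of the three planned splits are harmless to the pairing, because monozygotic co-twins have the same sex and age. The mass split is different. The study selects pairs for a BMI gap, and selection on a gap pushes co-twins to opposite sides of any BMI threshold. When that happens, one twin goes into one analysis and the co-twin into the other.

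Two things are at stake. First, the heavier-versus-leaner comparison of training response within each subset loses the split pairs as within-pair evidence. Their members stay in the model as single twins, so part of the comparison is made between families. Second, separate models yield separate p-values. A reader can then take a significant change in one subset and a non-significant change in the other as a difference between obese and non-obese participants, which neither model has tested.

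**Working it through.** **Base number of pairs.** From Participants: 54 pairs invited, 25% not taking part or not eligible, another 25% dropping out. 54 × 0.75 × 0.75 = 30.4, which reproduces the article's 30 completing pairs.

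**Which twin goes where.** Let H and L be the BMI of the heavier and leaner twin, H ≥ L, with cut-off c. A pair is split when L < c ≤ H. The heavier twin is then always in the obese subset and the leaner always in the non-obese one. If L ≥ c, both twins are in the obese subset; if H < c, both are in the non-obese subset. Hence every single twin in the obese subset is a heavier twin, and every single twin in the non-obese subset is a leaner twin.

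**Share of pairs split.** The documents give no BMI distribution and no c, so this is an assumption shown as a range. Take c = 30, L normal with mean 24–32 and SD 3–5, a gap of 2 plus an exponential amount (mean gap 3–7), and H > 25. Simulating 400,000 pairs per combination gives:

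| Leaner twin mean / SD | Mean gap | Split | Both obese | Neither obese |
|---|---|---|---|---|
| 24 / 3 | 3 | 20% | 3% | 77% |
| 26 / 4 | 5 | 45% | 18% | 37% |
| 26 / 3 | 7 | 61% | 10% | 30% |
| 30 / 4 | 4 | 32% | 51% | 17% |
| 32 / 5 | 3 | 19% | 67% | 14% |

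Over the whole grid the split share runs from 19% to 61%. Of 30 pairs that is 30 × 0.19 = 5.7 to 30 × 0.61 = 18.3, so about 6 to 18 split pairs and 12 to 24 intact pairs to divide between two subsets.

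**What the split does to the contrast.** Suppose a subset holds P intact pairs and S single twins, all on one side. With equal variances and within-pair correlation ρ, the mixed model gives the single twins a weight of (1 − ρ) × S / (S + P) in the mean for their side of the heavier-versus-leaner contrast. Three scenarios use a normal gap, kept if at least 2, with H > 25:

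| Leaner mean/SD, gap mean/SD | Split (S) of 30 | Both obese (P) | Neither obese (P) |
|---|---|---|---|
| 25/3, 5/2.5 | 53.8% ≈ 16 | ≈ 2 | ≈ 12 |
| 26/3.5, 4/2 | 46.4% ≈ 14 | ≈ 4 | ≈ 12 |
| 27/4, 6/3 | 56.2% ≈ 17 | ≈ 7 | ≈ 6 |

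In the first scenario, obese subset, ρ = 0.7: 0.3 × 0.538 / (0.538 + 0.050) = 0.27. Across the three scenarios and both subsets the single twins' weight is 16–27% at ρ = 0.7, 5–9% at ρ = 0.9 and 27–46% at ρ = 0.5. The Power calculation section quotes correlations over 0.7, 0.93 and 0.98; applying them to changes over time is a further assumption.

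**Imbalance.** In the same scenarios heavier twins make up 77–92% of the obese subset and leaner twins 68–79% of the non-obese one. The twin factor and the subgroup label are therefore largely aligned.

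**The case against.** Several points on the other side carry weight.

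- The analysis is optional and secondary. The main model keeps all pairs and answers the heavier-versus-leaner question there. This stands and limits the importance of the point. The size condition does not protect the pairing, though, because it concerns numbers, not pairs.
- The before/after change is within person, so each participant is his or her own genetic control in either subset. This stands. A reader might infer that the whole subgroup result is confounded by genes and family; the documents do not support that. Only the time x twin contrast is exposed, and only through split pairs.
- A reader might infer that co-twin control is lost, or that the contrast becomes mainly one between unrelated people. That is too strong. Pairs in the same obesity category stay intact, and with correlations of 0.7 or more the mixed model keeps most of the weight within pairs.
- A reader might also infer that about half of the pairs are split. That figure appears only under some assumed distributions, and pairs admitted on insulin resistance without a BMI gap would be split less often.
- The Participants section at one point describes the participants as twin pairs, and an article may leave cut-offs and interaction tests to a fuller document. Absence of those details is not the point. Elsewhere the word is used for individuals, and the text as it stands chooses separate analyses by participant, which conflicts with a within-pair twin factor.

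**Conclusion.** The point holds in a limited form. Followed as written, the mass subgroup separates every pair that straddles the obesity cut-off: roughly 20–60% of pairs, or 6–18 of 30, under assumed BMI distributions and an assumed cut-off of 30. In those subsets the time x twin estimate may rest on few intact pairs, about 2–7 in the obese subset in the three scenarios above, and draws partly on between-family information. Separate models give no test of whether the training effect differs by obesity. The consequences are imprecision, some mixing of within- and between-pair evidence, and an untested comparison. The training effect within each subset and the main analysis stand. The change is worth making because it is cheap, although the analysis concerned is secondary.

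**What to change.** Define the mass subgroup per pair from baseline BMI, for example heavier co-twin obese yes or no, and state the cut-off. Keep all pairs in one mixed model with time, twin and time x twin. Add subgroup x time, and subgroup x time x twin labelled exploratory, and report estimates with 95% confidence intervals instead of comparing p-values from separate models. No pair is then split. Sex and cohort do not break pairs, but differences between those subgroups should likewise be read from an interaction term.

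The cost is a sentence and a few model terms. The question shifts slightly, from obese individuals to pairs in which the heavier twin is obese. Precision will be limited: even with an equal 15/15 split of pairs and equal variances, the standard error of a subgroup difference is √(1/15 + 1/15) / √(1/30) = 2 times that of the corresponding effect in all 30 pairs, and the three-way term will be imprecise. That imprecision should be visible in the intervals.
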